### Setting

Patients will be recruited from approximately 20 NHS Trusts across the UK, including teaching and non-teaching hospital settings across England, Scotland and Wales. Patients will be identified and approached by members of their direct care team and will be given as much time as they need to make a decision about participation. Informed consent will be confirmed to the site’s principal investigator (PI) or a delegated sub-investigator. Patients who meet the eligibility criteria will be randomised.

Ten sites were initially approached to join the trial but this was expanded to 20 in September 2021 in order to address delays faced as a result of the COVID-19 pandemic. This expansion has allowed the trial to reach a larger pool of AAV patients. Sites with larger vasculitis clinics will be expected to recruit between 4 and 10 patients, with smaller community sites recruiting between 2 and 5 patients.

### Participants

Patients with ANCA-associated vasculitis (AAV) attending NHS vasculitis clinics will be approached by their direct care team to take part in the trial. Once the patient has provided consent, they will be screened against the following criteria:

#### Inclusion criteria

Are at least 18 years of age at screeningHave a clinical diagnosis of granulomatosis polyangiitis (GPA) or a diagnosis of microscopic polyangiitis (MPA) or a diagnosis of eosinophilic granulomatosis with polyangiitis (EGPA) according to the Chapel Hill Consensus Conference DefinitionsHave a Birmingham Vasculitis Activity Score (version 3) [23] > 3 with minor BVAS items only (no major BVAS items). BVAS should be > 3 at screening and at randomisationPatients should be receiving maintenance therapy at a stable dose for 4 weeks prior to randomisation. Maintenance therapy is defined as prednisolone and/or azathioprine, methotrexate, mycophenolate, co-trimoxazole or maintenance rituximab therapyPatients receiving corticosteroids for reasons other than vasculitis must be on a stable regimen for 4 weeks prior to randomisationA female patient is eligible to enter the study if she is:Not pregnant or nursingOf non-childbearing potential (i.e. women who have had a hysterectomy, are postmenopausal, defined as ≥ 1 year without menses, have both ovaries surgically removed or have documented tubal ligation or other permanent sterilisation procedure); orOf childbearing potential. These women must have a negative urine pregnancy test at screening and at baseline and be using at least one effective method of contraception

Periodic abstinence (e.g. calendar, ovulation, symptothermal, post-ovulation methods) and withdrawal are not acceptable methods of contraception. Consistent and correct use of one of the following acceptable methods of birth control for 1 month prior to the start of the study agent, during the study and 16 weeks after the last dose of study agent:Oral contraceptive, either combined or progestogen aloneInjectable progestogenImplants of levonorgestrel or etonogestrelEstrogenic vaginal ringPercutaneous contraceptive patchesIntrauterine device (IUD) or intrauterine system (IUS) with < 1% failure rate as stated in the product label7.No contraindications to hydroxychloroquine therapy8.Willing and able to give written informed consent to participate in the trial9.Patients should have sufficient English in order to provide informed consent and complete the patient questionnaires

#### Exclusion criteria

Patients currently taking hydroxychloroquine or related antimalarial such as mepacrine or chloroquinePatients with estimated glomerular filtration rate (eGFR) < 30 ml/minPatients weighing < 40 kgSensitivity, anaphylaxis or allergy to hydroxychloroquine or any other 4-aminoquinoline compoundKnown glucose 6 phosphate dehydrogenase deficiencyKnown lactose intoleranceEvidence of plaque psoriasisConcomitant use of the following medications within the last 6 months:Tumour necrosis factor inhibitor treatment (e.g. etanercept)CyclophosphamideAbataceptAlemtuzumabAny experimental or biological therapiesIntravenous, intramuscular or sub-cutaneous immunoglobulinPlasma exchangeAntithymocyte globulinTamoxifenLive vaccinesB cell depleting therapy (rituximab) for remission induction within the last 6 months. Rituximab maintenance therapy is permittedSevere or rapidly progressive ANCA vasculitis with at least one major BVAS itemHave clinical evidence of significant unstable or uncontrolled acute or chronic diseases not due to vasculitis (i.e. cardiovascular, pulmonary, hematologic, gastrointestinal, hepatic, renal, neurological, malignancy or infectious disease) which, in the opinion of the principal investigator, could confound the results of the study or put the patient at undue riskPatients taking long-term macrolide antibiotics for a chronic condition. This does not include topical preparationsHave a history of malignant neoplasm within the last 5 years, except for adequately treated cancers of the skin (basal or squamous cell) or carcinoma in situ of the uterine cervixHave current drug or alcohol abuse or dependence or a history of drug or alcohol abuse or dependence within 364 days prior to randomisation. A urine drug screen should be performed and confirmed negative prior to study entryHave active hepatitis B, hepatitis C or HIV-1. Patients with positive hepatitis B core antibodies may be eligible providing the viral load is undetectable and/or the patient is receiving prophylactic antiviral agentsHave a grade 3 or greater laboratory abnormality based on the Common Terminology Criteria for Adverse Events (CTCAE) toxicity scale (version 5), unless considered by the investigator to be related to the underlying disease or induction therapyScreening 12-lead electrocardiogram (ECG) that demonstrates clinically relevant abnormalities that may affect patient safety or interpretation of study results, including: QT interval corrected using the same consistent formula at each visit (QTc) > 470 msec for female > 450 msec for male patients demonstrated by at least two ECGsParticipation in any other interventional trial within the last 6 monthsHave a current symptomatic COVID-19 infectionHave been admitted to the ICU in the past 6 months due to a COVID-19 infection

At trial entry, eligible participants will have uncontrolled disease, which is defined as BVAS > 3. Over the course of the study, a participant may have a limited or severe flare, persistent disease, or they may enter remission. A limited flare is defined as a new or worsening minor item on the BVAS with no new major items, whereas a severe flare includes a new or worsening major item. Persistent disease indicates the presence of one or more ongoing items on the BVAS with no new or worsening items, while remission is defined as a BVAS of 0 on two consecutive visits planned to be at least 4 weeks apart.

### Intervention

Participants will be blinded and receive either 400mg daily hydroxychloroquine or placebo tablets taken orally in addition to standard of care therapies. The dose will be reduced to 200 mg daily for the duration of the trial for patients who weigh < 50 kg or who have an eGFR of 30–50 ml/min.

After study treatment, participants whose eGFR dropped below 60 ml/min at any point of the trial will be asked to attend an optometrist appointment to assess near visual acuity and visual fields.

Participants will be withdrawn from the investigational medicinal product (IMP) if they develop end stage renal failure, require a critical care admission, or if they are admitted to hospital with a COVID-19 infection. The patient may resume treatment once recovered if admitted due to COVID-19. The PI may also discontinue treatment in the event of an adverse event (AE) in accordance with best medical judgement and patients may ask to withdraw from the trial at any time.

Participants will be asked to return any unused IMP and/or empty packaging at each trial visit. The study drug returns will be returned to pharmacy for accountability. Participants will also be prompted to complete a weekly diary to record compliance. If compliance is ≤ 80%, the investigator should counsel the patient and ensure steps are taken to improve compliance. Any instances of a patient with > 120% compliance (considered an overdose) will be escalated to the trial management group (TMG) and the trial steering committee (TSC) in addition to the patient receiving counselling. Secondary levels of monitoring are provided by the DMC as part of interim data reviews and blood hydroxychloroquine levels.

Blood samples will be collected at four visits across the trial in order to analyse the levels of hydroxychloroquine in the blood. This analysis will be completed after the trial has ended to maintain blinding to treatment allocation. Samples will also be collected and stored for future research into AAV.

### Randomisation and blinding

Participants will be randomised 1:1 to the intervention or placebo with minimisation for ANCA (positive vs negative), age (</≥ 60 years), previous rituximab therapy (yes/no) and smoking (current smoker/non-smoker) to ensure balanced groups. Authorised staff members at each trial site will recruit participants and enter their details into a web-based randomisation system hosted by King’s Clinical Trial Unit (KCTU) to obtain treatment allocation. Blinded allocation details will be sent by email automatically to key trial site staff.

Both participants and research staff will be blinded to treatment allocation. Only the data monitoring committee (DMC) will have access to unblinded data during the trial period to safeguard patient interests. Blinded treatment supplies with unique treatment pack identifiers will be allocated through the King’s Clinical Trials Unit Intervention Management System. Evidence of unblinding of research staff completing data collection will be investigated.

Emergency code breaking services will be provided by ESMS Global with services available 24/7. Direct care teams and clinical trial personnel are permitted to receive unblinding information in the instance that the medical care of the patient is dependent on knowing the treatment allocation. Where possible, the PI will be contacted to confirm whether unblinding is necessary.

### Outcome measures

The primary outcome is the proportion of patients at any point during the final 12 weeks of the study (± 7 days) with uncontrolled AAV disease activity (defined as BVAS > 3) OR with controlled AAV disease activity (BVAS ≤ 3) but prednisolone dose for AAV > 7.5 mg daily OR with controlled AAV disease activity (BVAS ≤ 3) but any corticosteroid use > 7.5mg daily for any reason*.

The following secondary outcomes will be examined:Median cumulative number of visits where BVAS = 0 experienced by each patient (excluding screening, baseline and week 56)Proportion of patients with deemed treatment failure at week 52Mean cumulative dosage of prednisolone*Total number of adverse events per treatment arm*Median cumulative number of infections experienced by each patientMedian number of vasculitis flares (major and minor) experienced by each patient (excluding those as screening, baseline and week 56)Median time from randomisation to remission (BVAS = 0 on two consecutive visits at least 4 weeks apart)Median time to the first severe flare with starting time points of randomisation and remission (if achieved)Median time to the first limited flare with starting time points of randomisation and remission (if achieved)Proportion of patients categorised as having a severe flare at each time point (excluding screening, baseline and week 56)Proportion of patients categorised as having a limited flare at each time point (excluding screening, baseline and week 56)Median absolute Vasculitis Damage Index (VDI) [24] at each time point and the median relative change in VDI from baseline to each time point

The following exploratory outcomes will be examined:Proportion of patient with incidence of new diabetes mellitus*Proportion of patients with dyslipidaemiaMedian Functional Assessment of Chronic Illness Therapy (FACIT) [25] score at each time point and the median relative change in FACIT score from baseline to week 52/56*Median scores in quality-of-life measures: SF-36 [26], EQ5D [27], Health Assessment Questionnaire (HAQ) [28] and AAV Patient Reported Outcome (PRO) [29] at each time point and the median relative change in the same quality of life measures from baseline to week 52/56*Median Glucocorticoid Toxicity Index (GTI) [30] at each time point and the median relative change in GTI from baseline to week 52/56Median Physician’s Global Assessment (PGA) [31] at each time point and the median relative change in PGA from baseline to week 52/56*Mean ANCA titres at each time point and the median relative change in ANCA titres from baseline to each time point*Proportion of patients with medicine compliance of ≤ 80%Mean absolute values and relative change from baseline to each time point in renal variables: serum creatinine, serum albumin, urine protein to creatinine ratio*

Participants wishing to stop trial medication will be asked to continue trial visits and data collection if willing. Otherwise, they will be withdrawn from the trial.

In the case that a participant withdraws more than 4 weeks since their last hospital visit, they will be invited to attend a withdrawal visit or a telephone interview. Data contributing to the asterisked (*) outcome measures above will be collected if feasible during this visit. Data collected prior to participant withdrawal will be included in the statistical analysis where possible.

It is anticipated that the withdrawal rate for this cohort of patients will be < 5% [21, 32, 33]. No specific plans have been made to ensure participant retention as this low withdrawal rate is based on similar studies in AAV patients. However, participants will be contacted via the telephone between hospital visits which are longer than 4 weeks apart to provide regular contact and encourage participants to report AEs.

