## Methods

### Trial design

The HAVEN trial is a double-blind, placebo-controlled multi-centre trial following a phase II selection design. Participants will be randomised to receive hydroxychloroquine or placebo in a 1:1 ratio, in addition to standard of care (SoC) maintenance therapy with prednisolone and/or stable doses of azathioprine, methotrexate, mycophenolate, co-trimoxazole or maintenance therapy with B cell depleting therapy (rituximab). Each patient will be treated with adjunctive hydroxychloroquine 400 mg daily or matching placebo for 52 weeks with dose reduction according to actual body weight and renal function. Participants will attend 10 visits across 60 weeks (Fig. 1). At each visit, disease activity will be determined using the Birmingham Vasculitis Activity Score (BVAS), and data will be collected on other measures including further disease activity indicators, treatment adherence, clinical biomarkers and quality of life (Table 1).

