### Statistical analysis

Due to the use of a selection theory (pick the winner) approach, the main analysis will not include inferential analysis. Instead, the main analysis will involve presenting the descriptive statistics for each treatment arm to demonstrate which treatment is selected (i.e. which treatment group has a lower proportion of participants meeting the primary endpoint criteria). Due to this trial design, no interim analyses have been planned.

The descriptive statistics follow those specified in the outcome measures. The primary outcome and secondary/exploratory outcomes specifying a proportion will be described as the number and proportion of participants meeting that outcome. Secondary/exploratory outcomes specifying median will be described as median and range. Secondary/exploratory outcomes specifying mean will be described as mean and standard deviation.

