## Discussion

This trial aims to investigate whether the administration of hydroxychloroquine in addition to standard of care maintenance therapy can improve the clinical response of AAV by moderating disease activity, reducing disease flares and preventing disease progression, culminating in an improved quality of life for patients with this disease. The importance of developing additional treatment options for AAV cannot be understated. Although a recent meta-analysis has demonstrated a decline in mortality risk (likely due to improvements in therapeutics and patient care) [2, 35, 36], the mortality within this population is still approximately double that of the general population. Alongside this, both physical and mental quality of life for this cohort is poor compared to the general population [37], and there is little evidence that this has improved under the more recent therapeutic developments [20].

Systemic vasculitis, including AAV, is associated with increased healthcare costs due to increases in hospital care and expensive medications [4, 38, 39]. Biological therapies used for relapsing AAV cost in excess of £6000 annually per patient. On an individual level, chronic autoimmune rheumatic disorders have been associated with higher unemployment, particularly as disease duration increases [40]. AAV is unlikely to be an exception with patient reports of reduced income and hindered careers [4, 40] as a result of their disease. The increasing cost of living in the UK means that new treatments that improve patient quality of life and ability to work are greatly needed for these patients. Alongside this, the NHS has seen a decade of budget cuts, which means that inexpensive treatments would reduce the healthcare burden of these patients. Hydroxychloroquine has the benefit of being a relatively cheap medication with an estimated cost of < £70 annually per patient and it has been shown to modify disease trajectory in other related-autoimmune conditions [8–11], including SLE. Shared immunopathology between AAV and these more common autoimmune conditions suggests that Hydroxychloroquine could be just as beneficial in this patient cohort.

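### Time to flare counted from remission compares subsets formed after randomisation; only the randomisation start point should be compared between arms

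*Protocol article*

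**What the plan says.** The Outcome measures section of the protocol article lists two flare-timing outcomes, each with two start points: "Median time to the first severe flare with starting time points of randomisation and remission (if achieved") and "Median time to the first limited flare with starting time points of randomisation and remission (if achieved"). The same list contains "Median time from randomisation to remission (BVAS = 0 on two consecutive visits at least 4 weeks apart"), so remission is an outcome in its own right.

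The disease-state paragraph that closes the eligibility criteria says: "At trial entry, eligible participants will have uncontrolled disease, which is defined as BVAS > 3". It also says that "remission is defined as a BVAS of 0 on two consecutive visits planned to be at least 4 weeks apart". Treatment lasts 52 weeks, and the last visit in Table 1 is at week 56.

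On analysis, the Statistical analysis section says: "Secondary/exploratory outcomes specifying median will be described as median and range". The Subgroup/exploratory analyses section adds unpaired t-tests or Mann-Whitney U tests for outcomes that are not proportions, at a one-sided 10% level, to flag results of potential interest. It makes no exception for the remission start point. The Discussion gives the aims as "moderating disease activity, reducing disease flares and preventing disease progression".

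**The concern.** Nobody is in remission at randomisation, so the set followed from remission is formed entirely afterwards, by an event the drug may bring about. Two things then differ between the arms.

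- **Who is in the set.** If the drug works, its remitters include patients who would not have remitted on placebo. If those are harder cases, they may also relapse more easily.
- **How long they are watched.** Follow-up ends at a fixed week, so patients who remit earlier have longer in which a flare can be seen.

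A censored-data method can deal with the second difference but not the first. What is at stake is the secondary evidence on reducing flares: time from remission to flare reads naturally as evidence on keeping patients well, and a planned between-arm test could flag it.

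**Working it through.** **1. The plan's own figure.** The only design calculation is for the primary outcome: 36 per arm, 50% v 35%. Exact binomial: P(fewer events on hydroxychloroquine) = 0.881 and P(tie) = 0.041, so 0.881 + 0.041/2 = 0.902. Normal approximation: Φ(0.15/√((0.25 + 0.2275)/36)) = Φ(1.30) = 0.904. Then 72/0.95 = 75.8, rounded up to 76. The stated 90% and 76 reproduce. No figure is given for time to flare, so all rates below are assumptions.

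**2. Time at risk.** Visits with BVAS fall at weeks 4, 16, 28, 40, 44, 48, 52 and 56. Remission confirmed at weeks 44 to 52 leaves 8 to 0 weeks before week 52, or 12 to 4 weeks if week 56 counts. The flare counts and proportions exclude week 56; the time-to-flare entries do not say.

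**3. Selection alone, by hand.** Assume 40% remit in either arm, with flare hazard 0.015 per week, and a further share *s* remit only on the drug, with *r* times that hazard. The drug has no effect on flares.
- Placebo, flare by 36 weeks after remission: 1 − exp(−0.54) = 41.7%. Median: ln 2/0.015 = 46 weeks.
- Drug, *s* = 15%, *r* = 2: (0.40 × 0.417 + 0.15 × 0.660)/0.55 = 48%.
- Drug, *s* = 30%, *r* = 3: (0.40 × 0.417 + 0.30 × 0.802)/0.70 = 58%.
- The drug-arm median falls to between 38 and 28 weeks.

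With a true flare hazard ratio of 0.8, the same two cases give 41.3% and 51.2% against 41.7%: a real benefit is hidden or reversed.

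**4. Time at risk alone.** In a simulation where all patients have the same risk, remission is three times as fast on the drug and flares are unaffected, mean follow-up after remission is 29.2 weeks on placebo v 34.7 on the drug. Kaplan-Meier flare at 24 weeks is equal (25% v 25%). Crude flare is 28.9% v 33.5%, so the drug looks worse. Median time among those who flare is 13.6 v 15.7 weeks, so the drug looks better.

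**5. A censored-data method under selection.** Now let risk vary between patients (log-normal, log-SD 1), with a true flare hazard ratio of 0.8. Kaplan-Meier flare at 24 weeks after remission:

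| Remission rate on drug relative to placebo | Placebo | Drug |
|---|---|---|
| ×1 (no selection) | 20.5% | 17.2% |
| ×2 | 20.5% | 19.2% |
| ×3 | 20.5% | 20.9% |

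With ×3 and no flare effect at all, it is 20.6% v 25.0%.

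**6. Both together.** Severity *z* ~ Gamma(shape 2, scale 0.5); weekly remission hazard 0.015*m*/(*z*^1.5 + 0.05); flare hazard in remission 0.02*k z*^1.5; follow-up to week 52. Placebo has *m* = *k* = 1; the drug has *m* = 2, *k* = 0.9.

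| Measure | Placebo | Drug |
|---|---|---|
| Remission by week 52 | 61.5% | 78.0% |
| Mean severity of remitters | 0.71 | 0.80 |
| Flare among remitters | 28.3% | 32.1% |
| Flares per week in remission | 0.0100 | 0.0107 |
| Kaplan-Meier flare at 24 weeks | 23.6% | 25.2% |
| Median weeks, those who flare | 13.0 | 13.7 |
| Median weeks, all observed times | 29.5 | 33.0 |
| Remitted and flare-free, all randomised | 44.1% | 53.0% |

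Variations in the same model:
- No flare effect (*k* = 1): flare among remitters is 34.4% on the drug, yet the median among those who flare is 13.0 v 13.5 weeks.
- *k* = 0.8: rate 0.0100 v 0.0096 and Kaplan-Meier 23.6% v 23.0%. The benefit is diluted, not reversed.
- *m* = 1.3, *k* = 0.9: crude flare 28.3% v 28.4% (hidden), rate 0.0100 v 0.0097 (diluted).

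**The case against.** The strongest reply is about consequence. A reader might infer that a misleading relapse result would feed into the decision on an extended study. The documents do not support that: the Sample size calculation and Statistical analysis sections choose the winner on the primary outcome alone, and the Discussion ties an extended study to that same ranking. This part of the reply stands.

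A reader might also infer that the outcome is biased against the drug. That is too strong. The direction depends on the summary and on the assumed rates: crude flare and rate per week can count against a helpful drug, while the simple medians, which fit the planned median and range, moved in the drug's favour. An outright reversal needs a large remission effect beside a modest flare effect.

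An unselected comparison is already planned, since both outcomes also start at randomisation and flare counts and proportions cover everyone. The from-remission version is openly marked as conditional. With 36 per arm, the model in step 6 gives about 36 × 0.615 × 0.283 = 6 flares on placebo and 36 × 0.780 × 0.321 = 9 on the drug, too few for a difference of this size to be detected reliably. All this limits the weight of the point. It does not answer it: the article fixes the conditional start point and sets a test beside it without exception, and no analysis method restores the randomised comparison. A statistical analysis plan that is not shown could add a caution, but the outcome definition would still create the contrast.

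**Conclusion.** The point holds as a flaw in a secondary outcome. Time to flare from remission is not a randomised comparison and should not be tested as one. It can dilute, hide or reverse a true effect on flares, or produce one where none exists, and neither the direction nor the size can be known beforehand.

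The figures are illustrative. They assume that patients who are slower to remit also flare sooner, that the drug raises the remission rate 1.3- to 3-fold, and, in the simulations, one type of flare observed continuously rather than at visits. If remission rates are the same in both arms, the distortion is absent in these models. The primary outcome, the choice of winner and the flare outcomes measured from randomisation are untouched.

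**What to change.** In Outcome measures, make randomisation the only start point for comparing arms on time to first severe flare and time to first limited flare. Label any from-remission figure as description within each arm, and exempt it from the tests in Subgroup/exploratory analyses. State whether week 56 counts for the time-to-flare outcomes.

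To keep a measure of relapse after remission, add the proportion of all randomised participants who reach remission and stay flare-free to week 52, with non-remitters counted as no.

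The data are already collected; the cost is a change to outcome and analysis wording in a trial that is already recruiting. One planned secondary comparison becomes descriptive. The added proportion mixes reaching remission with keeping it: in the model of step 6 with no flare effect it still rises, from 44.1% to about 0.780 × (1 − 0.344) = 51%. It should be read beside time to remission and not as an effect on flares alone.

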**Research Blood Specimens:**														
Hydroxychloroquine levels		X			X		X					X		
Plasma, Serum and Cells^xiv^		X			X		X		X			X		X^xv^

^i^ Patients will be followed up by telephone at weeks 10, 22 and 34 rather than visiting the study centre. The phone call will be structured using the AAV pro questionnaire. See section 6.13 for more details

^ii^ To be arranged if a patient withdraws from the trial but is willing to have a final study visit. This is only necessary in instances where the patient’s last visit was more than 4 weeks ago

^iii^ The eye screen is only required for patients whose eGFR drops below 60ml/min at any point during the trial. The eye screen should take place between week 52 and week 56 visits by a local optometrist

^iv^ The eligibility criteria require BVAS to be scored and for female patients to have a pregnancy test at baseline as well as screening. Other screening procedures do not need to be repeated

^v^ Vital signs to include BP, pulse, respiration rate and temperature

^vi^ BVAS and VDI to be scored locally following training. BVAS scores will be quality checked by a central adjudication panel to ensure consistency

^vii^ Telephone follow up interviews will only use the AAV Pro questionnaire to structure the conversation. The SF-36, EQ5D and HAQ questionnaires will not be included

^viii^ Where ESR is not available, plasma viscosity may be used instead

^ix^ If the patient’s eGFR drops below 60ml/min at any point of the trial they should be invited for an eye screen between week 52 and 56

^x^ If the baseline visit is less than two weeks after screening, these tests do not need to be performed again

^xi^ Protein:creatinine ratio only needs to be performed if urine dipstick for protein shows 1+ or more, but results can be collected if routinely performed when the urine dipstick is negative

^xii^ Patients who test positive for hepatitis B surface antigen, hepatitis B core antibody, hepatitis C antibody or HIV-1 will be excluded

^xiii^ Urine pregnancy test

^xiv^ Plasma and serum collected at all sites. Cells at Guy’s Hospital only

^xv^ Samples only collected if the patient is identified as having a flare

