#### Considerations

Loss to follow-up is not expected as trials in a similar cohort only had a < 5% drop-out rate [21, 32, 33]. However, individual time points may experience missing data due to logistical issues. The number and proportion of participants with missing outcome data at each time point will be reported. The main analysis for this trial only considers time points in the final 12 weeks of the trial. Changes in this endpoint at each of the four visits during this period will be investigated but there is likely to be a low variability across each visit. As a result, participants with missing outcome data in one or two visits are unlikely to substantially bias the results. A sensitivity analysis will be utilised to confirm the lack of bias due to missingness in these last 12 weeks.

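### The protein:creatinine ratio is required only after a positive dipstick, so its planned mean and change from baseline describe a subset selected on the outcome itself

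*Protocol article*

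**What the plan says.** Three parts of the protocol article bear on this.

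- **The statistic.** The exploratory list under Outcome measures includes "Mean absolute values and relative change from baseline to each time point in renal variables: serum creatinine, serum albumin, urine protein to creatinine ratio". The Statistical analysis section says that the descriptive statistics follow the outcome list, with mean and standard deviation where a mean is named.
- **The measurement rule.** Table 1 schedules the ratio at every clinic visit, but footnote xi qualifies this: "Protein:creatinine ratio only needs to be performed if urine dipstick for protein shows 1+ or more". The footnote adds that "results can be collected if routinely performed when the urine dipstick is negative".
- **Missing data.** The Considerations section states: "The number and proportion of participants with missing outcome data at each time point will be reported". It also states: "A sensitivity analysis will be utilised to confirm the lack of bias due to missingness in these last 12 weeks". It attributes missed time points to logistical problems.

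Relative change is also named elsewhere. The secondary Vasculitis Damage Index (VDI) item pairs the level at each time point with "the median relative change in VDI from baseline to each time point". An exploratory item asks for "the median relative change in ANCA titres from baseline to each time point". ANCA-negative participants are expected, because randomisation uses "minimisation for ANCA (positive vs negative") as one of its factors.

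**The concern.** The measurement rule and the statistic do not fit together. A visit with a negative dipstick may yield no ratio, so the value is missing because it is low. The dipstick is read after randomisation, so the missingness can differ between arms if treatment affects proteinuria. The mean at each visit is then taken mainly over participants who still have proteinuria.

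The change from baseline is narrower still, since it needs a ratio at both ends. Someone whose proteinuria clears has no follow-up value, and someone who develops new proteinuria may have no baseline value. These are the two groups in whom the outcome moves most.

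The optional negative-dipstick results do not repair this. They would come from whichever of about 20 sites happen to measure the ratio routinely.

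At stake is the reading of one exploratory renal outcome, which the protocol also opens to a one-sided 10% test for results of potential interest.

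The relative-change wording raises a smaller, separate question: what the statistic means when the baseline is zero or undetectable.

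**Working it through.** **Inputs from the documents.** 36 per arm (Sample size calculation); the ratio required only at dipstick 1+ or more (Table 1, footnote xi); mean and relative change at each time point (Outcome measures). The plan gives no figure for the ratio. Its only sample size figure, 90% probability of correct ranking, reproduces: Φ(0.15 / √((0.25 + 0.2275)/36)) = 0.904. It does not depend on this outcome.

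**Step 1: can selection change the ranking?** Take four follow-up ratios per arm, measured only at 30 or above (invented values).
- Arm A: 10, 20, 40, 80. Full mean 150/4 = 37.5; measured-only mean (40 + 80)/2 = 60.
- Arm B: 10, 10, 10, 80. Full mean 110/4 = 27.5; measured-only mean 80.

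B is better on complete data and looks worse on measured data. This shows possibility, not likelihood.

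**Step 2: the systematic effect.** All inputs here are assumed: log-normal ratio with median 20 and log-SD 1, baseline to follow-up correlation 0.7, dipstick positive above 30, very large sample.
- Uniform benefit, every treated ratio multiplied by exp(−0.4): full means 33.1 v 22.1, a reduction of 1 − 22.1/33.1 = 33%. Measured-only means 69.8 v 60.8, a reduction of 1 − 60.8/69.8 = 13%. The order is kept and the contrast shrinks.
- Benefit confined to milder cases, ratios below 60 multiplied by exp(−0.6): full means 33.0 v 24.9; measured-only means 69.7 v 100.8. The order reverses.

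**Step 3: 36 per arm.** Same assumed model with a uniform benefit, 40,000 simulated trials per row, and no optional ratios collected after a negative dipstick.

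| Assumed threshold | Benefit | Ratios available, placebo / treated | Treated with baseline and follow-up | Better arm has lower mean: all ratios | Same: measured only | The two rank oppositely |
|---|---|---|---|---|---|---|
| 20 | exp(−0.2) | 18.0 / 15.2 | 11.9 | 75.3% | 63.0% | 19.5% |
| 20 | exp(−0.4) | 18.0 / 12.4 | 10.2 | 91.3% | 73.1% | 20.0% |
| 30 | exp(−0.2) | 12.3 / 9.8 | 7.0 | 75.4% | 59.9% | 24.2% |
| 30 | exp(−0.4) | 12.3 / 7.6 | 5.8 | 91.1% | 68.4% | 25.1% |
| 50 | exp(−0.2) | 6.5 / 4.7 | 2.9 | 75.6% | 57.4% | 29.4% |
| 50 | exp(−0.4) | 6.5 / 3.4 | 2.3 | 91.0% | 63.8% | 30.1% |

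The better arm contributes fewer ratios in every row.

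**Step 4: relative change.** On the ordinary reading, (follow-up − baseline)/baseline, a baseline of zero gives no value, and an undetectable titre gives one fixed by the assay floor. That applies to ANCA-negative participants. For a score that can start at zero, take six invented participants per arm with baselines 0, 0, 0, 2, 2, 4.
- Arm A follow-up 0, 0, 1, 3, 2, 5: mean absolute change 3/6 = 0.50; relative changes where defined 0.50, 0, 0.25, median 0.25.
- Arm B follow-up 2, 2, 1, 2, 2, 4: mean absolute change 5/6 = 0.83; relative changes where defined 0, 0, 0, median 0.

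B accrues more damage but looks better on the relative measure.

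**The case against.** The strongest reply has four parts.

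1. **Optional values.** Footnote xi lets negative-dipstick ratios be collected, so the subset need not be purely dipstick-positive. This stands as a limit on size: the simulation assumes that none are collected. It does not remove the selection, because collection follows local habit.
2. **Missing counts will be reported.** True, and the reduced denominator would be visible. Disclosure does not correct a mean that is missing its low values. The promised sensitivity analysis is tied to the last 12 weeks of the main analysis.
3. **Reversal.** A reader might infer that the plan will make an effective treatment look harmful. The documents do not support that: they give no distribution for the ratio, and a uniform benefit is attenuated, not reversed. Systematic reversal needs an effect concentrated in milder cases. The opposite rankings in Step 3 are chance mis-rankings in small samples.
4. **Relative change is not defined here.** The term absolute in these items describes the level at a visit, so relative change could mean a simple difference, and the formula may sit in a document not shown. This stands, and the second point is therefore conditional. Nor does it reach creatinine, albumin or a measured ratio, none of which is plausibly zero. The documents do not give the ranges of VDI or the other scores, or how a negative ANCA result is recorded.

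**Conclusion.** The mismatch over the protein:creatinine ratio is established from the protocol's own text. Followed as written, the plan averages a subset chosen by the post-randomisation value of the outcome. The expected consequence is attenuation and a raised chance of mis-ranking the arms. The size depends on assumptions: under those tried, correct ranking falls from 75-91% to 57-73%.

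The relative-change point is secondary and conditional on division by baseline. It has document support for ANCA titre, because ANCA-negative participants are enrolled. For VDI it holds only if the baseline can be zero. A reader might infer that new damage from a zero baseline vanishes from the VDI outcome. It does not, because the same item also reports the VDI level at each time point, so only one of its two components is affected. No count of affected participants can be given, since the documents state neither the share who are ANCA-negative nor the share with a zero score.

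The reach is limited to exploratory outcomes and one component of a secondary outcome. The primary outcome, the selection rule and the sample size are untouched.

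**What to change.** Settle the following in wording before unblinding.

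- **Ratio.** Classify a dipstick-negative visit without a ratio as below threshold. By arm and visit, report the proportion with dipstick 1+ or more (or with a ratio at or above a fixed value), and the median with below-threshold values ranked lowest. If more than half are below threshold, the median is reported as such and the proportion carries the information. Say how optional ratios from negative-dipstick visits are used, so that the result does not turn on site habit. Label any mean of measured ratios as conditional on a positive dipstick, with its denominator.
- **Relative change.** Define it. For ANCA titre, report it only in participants positive at baseline. For VDI and any other score whose baseline can be zero, use absolute change from baseline.

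The cost is small: slightly more analysis work and the loss of a simple mean for the ratio. No new test is needed, because Table 1 already schedules a urine dipstick at every clinic visit; this assumes that the protein result is captured in the trial data.
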